##### Exercises

Each training session will last 30 min with a focus on lower limb muscle strengthening as well as balance. Sessions will start with 5 min of activation (walking on a treadmill or cycling). Then, participants will be asked to complete 5 exercises targeting lower limb strengthening (time: 18 min) followed by 2 exercises designed to improve balance and 3 stretching exercises for the lower limb (time: 7 min). Levels of difficulty for each exercise will vary according to the patient’s capacity to ensure that each exercise is appropriate and safe while allowing a progression over time.

##### Education

Education will consist of two one-on-one sessions (during week 2 and week 4 assessments) during which participants will receive information directly related to LSS and NC using pre-recorded standardized videos developed for the study. This information consists of explanations of the pathophysiology of LSS and NC as well as expected natural history, usual symptoms, pain management strategies for daily living (body positioning when walking and when sleeping), and physical activity recommendations. Illustrations and videos will be used to enhance participants’ understanding and to ensure a standardized delivery of education. Participants will also be invited to ask questions. Each session will last for 20 min.

#### Control croup

The participants in the control group will only receive the education sessions at week 2 and at week 4.

##### Participant trajectories

Regardless of group allocation, all participants will continue to follow their usual care routine. Usual care can include general advice for daily living; advice to stay active; oral medication to control pain, inflammation, or mood; and a referral for a spinal injection. Their treatments will be monitored throughout the study duration.

### Data collection

Participants will be evaluated five times during the study (baseline, week 2, week 4, week 6, and week 12). Each assessment will include both patient-reported outcome measures (PROMs) and objective physical measures. All assessments will be conducted at the UQTR biomechanics laboratory. The data collection process is synthesized in Table 1. All participants will be called for a reminder before each assessment.

**Table 1 Tab1:** Data collection

	Measures	Baseline assessment	Week 2 assessment	Week 4 assessment	Week 6 assessment	Week 12 assessment
Baseline measurements	Sociodemographic data and physical examination	X	–	–	–	–
Primary outcome	SPWT	X	X	X	X	X
Secondary outcomes	NRS for leg pain intensity	X	X	X	X	X
	NRS for back pain intensity	X	X	X	X	X
	Leg pain dominance	X	–	–	–	–
	FC-SSSQ	X	–	–	X	X
	FC-CPSES	X	–	–	X	X
	FC-HADS	X	–	–	X	X
	QAPPA	X	–	–	X	X
	Gait pattern characteristics	X	X	X	X	X
	SPPB	X	–	–	X	X
	Global perceived change	–	X	X	X	X

*SPWT* Self-Paced Walking Test, *NRS* Numerical Rating Scale, *FC-SSSQ* French-Canadian adaptation of the Swiss Spinal Stenosis Questionnaire, *FC-CPSES* French-Canadian Chronic Pain Self-Efficacy Scale, *FC-HADS* French-Canadian adaptation of the Hospital Anxiety and Depression Scale, *QAPPA* Questionnaire d’activité physique pour les personnes âgées [Physical Activity Questionnaire for the Elderly], *SPPB* Short Physical Performance Battery

During the baseline assessment, participants will first complete a series of questionnaires and undergo a standardized physical examination. The questionnaires will include measures of age, sex, height, weight, leg pain dominance, and number of falls in the past 6 months. Participants will also be asked about the presence of comorbidities known to have a negative influence on walking capacity as well as previous conservative treatment (e.g., injection, manual therapy). The physical examination will include the assessment of lower limb dermatomes and myotomes as well as pallesthesia and osteotendinous reflexes (to document the absence of peripheral neuropathy).

### Primary outcome

The primary outcome of this study is walking capacity which will be assessed using the Self-Paced Walking Test (SPWT). The SPWT represents the current gold standard for assessing walking capacity in patients with LSS [9, 25]. During this test, participants will be asked to walk freely on a leveled surface at their own pace until they are forced to stop for a minimum of 3 s because of LSS symptoms. The time and distance reached by the participants will be measured. The minimal clinically important change (MCID) reported for the SPWT varies between 319 and 376 m [26]. As patients with LSS causing NC are at higher risk of falls, participants will walk near a ramp and a research assistant will also walk behind the participant during the walking test to assist if needed.

### Secondary outcomes

#### Patients-reported outcomes measures

Participants will be invited to complete a set of questionnaires assessing physical and psychological PROMs including leg and back pain (numerical rating scale) [27], LSS-related disability (French-Canadian version of the Swiss Spinal Stenosis) [28], self-efficacy (French-Canadian Chronic Pain Self-Efficacy Scale) [29], physical activity (Questionnaire d’activité physique pour les personnes âgées) [30], and anxiety and depression (French-Canadian adaptation of the Hospital Anxiety and Depression Scale) [31].

##### Leg and back pain

Leg and back pain intensity will be independently assessed using an 11-point Numerical Rating Scale (NRS) (0 indicating an absence of pain, 10 indicating the worst pain imaginable) [27].

##### Disability-related to LSS

LSS-related disability will be measured using an adapted version of the validated French-Canadian version of the Swiss Spinal Stenosis Questionnaire (FC-SSSQ) [28]. This questionnaire is a LSS-specific tool composed of three subscales which assess symptom severity, physical function, and satisfaction with care. The pain subscale includes seven items of which six are scored using a 5-point Likert scale, and one (Q7) is scored using 1, 3, or 5 points. The physical function subscale includes 5 items scored on a 4-point Likert scale. In the proposed study, the satisfaction subscale will be removed because no participants will have undergone surgery. For the symptom severity and physical function subscales, a higher score indicates greater disability, and the FC-SSSQ total possible score without considering the satisfaction subscale is 55 points. We considered that this outcome measure is the most appropriate for patients with LSS causing NC. In fact, the SSSQ has been established as the gold standard questionnaire to assess pain and function [32]. This questionnaire is also highly correlated with the SPWT [33], the standard criterion to assess walking capacity in patients with LSS causing NC [9].

##### Self-efficacy

Self-efficacy will be assessed using the validated French-Canadian Chronic Pain Self-Efficacy Scale (FC-CPSES) [29]. Each of its 33 items is measured using a 10-point numerical scale (1 = not at all confident and 10 = totally confident). The FC-CPSES total score ranges from 1 to 10 and is obtained by calculating the mean score of the 33 items. Higher scores indicate higher self-efficacy.

##### Physical activity

Physical activity level will be assessed using the validated *Questionnaire d’activité physique pour les personnes âgées* [Physical Activity Questionnaire for the Elderly] (QAPPA). This questionnaire assesses the amount of moderate and vigorous physical activity during the last 7 days (MET-min/week). Following the completion of this questionnaire, participants can be classified into the following categories according to their physical activity volume: high, moderate, or low physical activity level [30, 34].

##### Anxiety and depression

Anxiety and depression will be assessed using the validated French-Canadian adaptation of the Hospital Anxiety and Depression Scale (FC-HADS) [31]. This questionnaire is a 14-item scale with 7 items assessing anxiety and 7 items assessing depression. Each item is scored from 0 to 3 for a maximum of 21 points for each subscale. A higher score indicates higher anxiety (HADS-A) or higher depression (HADS-D).

##### Patients’ global impression of change

Patient’s global impression of change (PGIC) will be measured using a 7-point scale that ranges from “very much improved” to “very much worse” with “no change” as the mid-point [35, 36].

#### Objectives measures

##### Walking capacity and gait pattern characteristics

During the SPWT, two synchronized inertial sensors (Physilog®6 – GaitUp, Lausanne, Switzerland, 128 Hz) will be placed and attached on the top of each participant’s shoe. These inertial sensors include a 3-dimension accelerometer, gyroscope, and magnetometer which allow the measurement of more than 25 gait parameters including general (e.g., speed, left/right asymmetry, variability, and cycle duration), temporal (e.g., stance, swing, and double support), spatial (e.g., swing speed, swing width, and strike angle), and clearance (maximum heel, maximum and minimum toe clearance) parameters.

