**Methods/design:**

This is a prospective randomized controlled parallel-group clinical trial. Sixty-six patients with LSS causing NC will be recruited from identified clinics and local advertisements. The intervention group will receive standardized education and specific exercises while the control group will only receive a standardized education. The program in both groups will last for 6 weeks with 5 evaluation time points (baseline, week 2, week 4, week 6, and week 12). The primary outcome will be walking capacity measured with the Self-Paced Walking Test, and the secondary outcomes will be back and leg pain intensity, LSS-related disability, self-efficacy, level of physical activity, anxiety, depression, gait pattern characteristics, balance, and global perceived change.

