## Background

Neurogenic claudication (NC) is a clinical syndrome recognized as the hallmark of symptomatic lumbar spinal stenosis (LSS) [1], a degenerative musculoskeletal condition caused by age-related changes in the lower spine and defined as the narrowing of the spinal canal or intervertebral foramina [2, 3]. Neurogenic claudication is characterized by bilateral or unilateral buttock, thigh or leg pain, and discomfort such as numbness, tingling, and weakness [4–7]. These symptoms are exacerbated by prolonged standing or walking, and they are temporarily relieved by sitting and bending forward [1, 6]. Because of its symptomatology, especially during daily activities that require walking, NC represents one of the leading causes of pain and disability in the elderly [8].

Over the past years, decreased walking capacity in patients with LSS causing NC, measured in time or distance, has been well documented using objective walking tests (treadmill and self-paced walking tests) [9, 10]. Moreover, a recent systematic scoping review reported that walking capacity was negatively associated with pain outcomes and disability [11]. In addition, greater disability scores were negatively associated with walking speed and stride length, two important gait pattern characteristics of LSS [11]. Patients consider walking capacity and pain to be the most bothersome consequences of NC. They also report that decreased walking capacity is responsible for disrupting their daily life activities (e.g., walking, social activities, household activities, sleeping, and lifting) [12]. Furthermore, the decline in walking capacity due to NC is reflected in an increase in inactivity. Adoption of such a sedentary lifestyle contributes to a decline in quality of life especially with respect to physical status [13, 14]. Previous studies showed that patients with LSS causing NC are less active than the general population over the age of 60 and individuals with hip or knee osteoarthritis, with approximately 82% of their time spent in sedentary behavior [13–15].

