### Statistical analyses

Baseline characteristics and outcome measures will be summarized with descriptive statistics for each group. Two-tailed independent sample *t* tests will be performed to compare group baseline characteristics. Paired factor analyses using analyses of covariance will be performed for each of the outcome measures (primary and secondary). Such analysis ensures that identified confounding factors do not influence intergroup differences. ANOVAs will be used to compare the evolution of walking capacity over weeks. An intention-to-treat method will be used, and missing data will be replaced using a multiple imputation method. No additional analyses (e.g., subgroup and adjusted analyses) are planned for this study. Statistical analyses will be conducted using SPSS statistical version 26 for the Windows software, and the level of significance will be set at a *p*-value ≤ 0.05.

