Another point to consider when assessing the effectiveness of any intervention is the primary outcome measure. To date, most studies using exercises as the main intervention for LSS used indirect measures of walking capacity such as functional capacity measured by the SSSQ or the Zurich Claudication Questionnaire (ZCQ), leg and back pain intensity, disability measured by the ODI or the global rating of change scale as their primary outcome [46, 48–50]. Considering that a decrease in walking capacity is considered one of the most bothersome consequences of LSS causing NC [12], direct measures of walking capacity using a self-paced walking test should be used when assessing the effectiveness of interventions on functional capacities.

Overall, having a flexible rehabilitation program combining lower limb strengthening and balance exercises should lead to an improvement in walking capacity for patients with LSS causing NC. In addition, it should increase self-efficacy and decrease anxiety. This will also provide patients with a conservative treatment option that takes into consideration the day-to-day fluctuation in symptom severity. To our knowledge, this is the first LSS-specific rehabilitation program providing standardized education and graded exercises aimed at improving walking capacity regardless of patients’ current healthcare trajectories.

This study protocol also presents innovative components. Indeed, by adding inertial wearable sensors during the SPWT walking evaluation, this study will provide original and accurate information about the gait pattern characteristics of patients with LSS causing NC. By monitoring the gait biomechanical parameters throughout the study, we will also be able to determine which ones are modified by exercises and how they are modified. This could eventually help researchers and clinicians better understand the patient’s biomechanical adaptations over time as well as the impact of specific exercises on walking capacity or gait pattern characteristics. Findings from this study may eventually lead to improvement in the evaluation and management of patients with LSS causing NC.

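### The plan's unadjusted 5% test on each outcome cannot support the Discussion's promise to identify which individual gait parameters exercise changes

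*Protocol article*

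**What the plan says.** The Abstract lists the gait outcome as a single item among the secondary outcomes: "gait pattern characteristics, balance, and global perceived change". Table 1 under Data collection marks it at every assessment, and the schedule reads "Participants will be evaluated five times during the study (baseline, week 2, week 4, week 6, and week 12".

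The section on walking capacity and gait pattern characteristics describes two synchronised inertial sensors "which allow the measurement of more than 25 gait parameters". It groups these as general, temporal, spatial and clearance parameters and gives examples of each. It does not name a key parameter or say how many will be analysed.

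Under Statistical analyses, "analyses of covariance will be performed for each of the outcome measures (primary and secondary" outcomes alike. One significance level, p ≤ 0.05, is set for the whole trial, no multiplicity control is mentioned, and additional analyses are ruled out. The only analysis across time points concerns the primary outcome: "ANOVAs will be used to compare the evolution of walking capacity over weeks".

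The Discussion, in its paragraph on the innovative parts of the study, says that by following the gait parameters over the trial "we will also be able to determine which ones are modified by exercises and how they are modified".

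**The concern.** Saying which parameters exercise modifies means giving a yes or no for each one. The only criterion in the article for that decision is p ≤ 0.05 in an analysis of covariance. Applied to a list of about 25 parameters, that criterion is likely to return one or more positive results when exercise has changed nothing, and the plan offers no way to tell these from real changes.

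What is at stake is the interpretation of a secondary outcome that the article presents as a new contribution and hopes will inform clinicians. A chance difference in, say, toe clearance or double support could be reported as an effect of the exercises. The walking-capacity hypothesis, the primary outcome and the sample size are not touched.

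**Working it through.** **The plan's own figure.** There is none to reproduce. The article gives no error rate for the gait parameters. Its one computed figure, 66 participants, concerns walking capacity and has no bearing here.

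**Inputs**
- Number of parameters, m: 25, the lower end of what the sensors can measure. The number to be analysed is not stated, so this is an assumption and is varied below.
- Level per test: 0.05, two-sided (Statistical analyses).
- Tests per parameter: one. This is the reading that assumes least.
- True effects: none. This is the reference case for counting false positives.
- Correlation between parameters: not given, so assumed values from 0 to 0.7 are used.

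**One test per parameter**
- Expected false positives = m × 0.05 = 25 × 0.05 = 1.25. Correlation does not change this number.
- Chance of at least one if independent = 1 − 0.95^25 = 0.723.
- Chance of at least two if independent (binomial) = 0.358; at least three = 0.127.

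**Allowing for correlation.** These results come from 20,000 simulated sets of 25 two-sided z-tests, with the same correlation between every pair and no true effect.

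| Assumed pairwise correlation | Mean false positives | Chance of at least one | Chance of at least three |
|---|---|---|---|
| 0 | 1.25 | 72% | 13% |
| 0.3 | 1.24 | 60% | 15% |
| 0.5 | 1.25 | 47% | 15% |
| 0.7 | 1.25 | 32% | 14% |

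Even the lowest chance of a false claim, 0.317, is about six times the nominal 0.05 (0.317 / 0.05 = 6.3).

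**If fewer parameters are analysed** (independent tests)
- 10 parameters: 10 × 0.05 = 0.5 expected; 1 − 0.95^10 = 0.40.
- 5 parameters: 5 × 0.05 = 0.25 expected; 1 − 0.95^5 = 0.23.

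**If each of the four post-baseline visits were also tested separately** (not stated in the protocol; an upper bound for 25 parameters)
- Number of tests = 25 × 4 = 100; expected false positives = 100 × 0.05 = 5.
- Chance of at least one if independent = 1 − 0.95^100 = 0.994.
- With correlation 0.7 both between parameters and between visits, the simulated chance of at least one is 64%.

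**The case against.** The strongest reply is that the article does not describe the analysis that the arithmetic assumes. More than 25 is what the device can measure, not a count of planned tests. Gait appears as one outcome, and nothing says that each sensor output is an outcome in its own right. The choice of parameters, the visit and the handling of multiplicity among secondary outcomes commonly sit in an analysis plan, which is not shown. Other sentences on gait are cautious and speak of what the data might eventually contribute.

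Much of this stands. A reader might infer that more than 25 parameters will each be tested at four visits and that several false discoveries will follow. The documents do not support that. The schedule fixes when gait is measured, not a test at each visit, and the only analysis over weeks is for walking capacity. Five expected false positives is therefore a conditional upper figure. "Several" also sits badly with one test per parameter, where three or more arise with a chance of only about 13% to 15%. True effects would lower the number of false positives further. The 72% requires independence, which is unlikely for linked measures such as stance, swing and cycle duration, so the lower figures deserve equal weight.

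What does not stand is that this is only missing detail. The article itself states both the threshold and the conclusion to be drawn, and the two do not fit. Reading gait as one outcome does not help, because saying which parameters change requires a result for each. If only a subset is analysed but is not fixed in advance, it can be chosen after the data are seen.

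**Conclusion.** The point holds in a limited form. An unadjusted 5% rule on every secondary outcome cannot support the Discussion's statement about individual gait parameters. With 25 parameters tested once each and no true change, 1.25 false positives are expected, and the chance of at least one is 72% if independent, falling to about 32% at a correlation of 0.7. These figures rest on three assumptions: that about 25 parameters are analysed, that none truly changes, and that the stated correlations apply. A short prespecified list would shrink the problem, but the article names none. It is not established that every visit will be tested or that several false findings will occur. This should be corrected, but it does not affect the primary comparison.

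**What to change.** In Statistical analyses, state that the individual gait parameters are exploratory and are analysed as one family with Benjamini–Hochberg control at a 5% false discovery rate, at one prespecified visit. Week 6, the end of the programme, is a natural candidate. Results at the other visits would be descriptive.

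Optionally, prespecify a short key list chosen by the sponsor. The Background mentions "walking speed and stride length, two important gait pattern characteristics of LSS", but it does so when reporting associations from a review, not when choosing outcomes for this trial. Speed is among the sensor examples and stride length is not, so the sponsor should confirm that the sensors output it. The visit and the list are suggestions; nothing in the article requires these particular choices.

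Reword the Discussion sentence to say that the study will explore which gait parameters may change with exercise.

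The cost is a few lines of text and code, with no new data. The price is stringency: with 25 parameters the step-up thresholds run from 0.05 / 25 = 0.002 for the smallest p-value to 0.05 for the largest, so fewer gait findings will be declared.

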##### Lower extremity physical function and balance

Lower extremity physical function and balance will be assessed using the Short Physical Performance Battery (SPPB), a validated test battery among older adults [37]. This test battery includes standing balance, 4-m walking at the usual pace, and repeated sit-to-stand tests. Each of the three tests of the battery is scored from 0 (inability to perform) to 4 (high category of performance) which puts the total score out of 12 (a higher score indicates lower extremity function). The standing balance test is divided into three components: side-by-side, semi-tandem, and tandem balance. For each component of the standing balance test, participants are asked to maintain the position for a maximum of 10 s. The 4-m walking test at the usual pace consists of walking at the usual pace on a leveled surface 4-m hallway. Participants will be asked to perform it twice, and the result of the fastest trial will be kept for analysis. The repeated sit-to-stand test consists of performing five sit-to-stand repetitions as fast as possible with arms across the chest. The score for this test is based on the time required to perform five repetitions. If participants are unable to complete five repetitions or if it takes more than 1 min to perform them, the score attributed to this test will be 0.

